#### Handling of confounding and selection bias

2.6.5

As treatment selection (dose choice) is made by the treating physician, confounding by indication is a potential concern when comparing outcomes across dose subgroups. Sensitivity analyses using propensity-score adjustment for baseline characteristics (age, sex, baseline LDL-C, cardiovascular risk category, prior lipid-lowering therapy, comorbidities) will be performed for dose-stratified analyses. Selection bias—arising from the voluntary nature of participation and the open-label design—is acknowledged as an inherent limitation and will be addressed by detailed reporting of consecutive screening logs, reasons for non-participation, and comparison of enrolled vs. screened-but-not-enrolled patients where data are available.

#### Anticipated attrition and loss to follow-up

2.6.6

Based on prior Korean real-world observational studies of lipid-lowering therapy, the anticipated attrition rate at Week 24 is approximately 10–15%, and at Week 48 approximately 20–25%. Participants lost to follow-up will be retained in the FAS using LOCF for the primary analysis, with sensitivity analyses as described in Section 2.6.4. Reasons for discontinuation will be systematically captured (e.g., adverse event, lack of efficacy, patient withdrawal, switch to alternative therapy, loss to follow-up).

### Laboratory measurements and quality control

2.7

Lipid panel (LDL-C, TC, TG, HDL-C, non-HDL-C) and safety laboratory tests (AST, ALT, CK) are performed at each participating center’s local laboratory using standard clinical assays. LDL-C may be measured either directly (by homogeneous direct assay) or calculated using the Friedewald formula. When TG ≥400 mg/dL, the Friedewald formula is invalid and direct LDL-C measurement is required; in such cases, non-HDL-C will be used as a supplementary measure. The LDL-C measurement method (direct vs calculated) will be recorded for every measurement and analyzed as a covariate. To address inter-laboratory variability, all participating laboratories must be certified under the Korean Laboratory Accreditation Scheme or equivalent national/international standards, and external quality assurance (EQA) results will be reviewed annually. Site-level training will be provided prior to study initiation, including standardized fasting requirements (≥12 hours preferred, ≥9 hours minimum for lipid and glucose testing), standardized variable definitions, and standardized data entry procedures. Electronic case report forms include built-in range and consistency checks. Independent monitoring visits will be conducted at high-enrolling centers, with remote source data verification at all sites. Discrepancies will be addressed through formal data queries.

### Therapeutic lifestyle counseling

2.8

All participants receive standardized Therapeutic Lifestyle Change (TLC) counseling at Visit 1, Visit 2, and Visit 3, in accordance with the 2022 KSoLA guidelines. Counseling content includes recommendations on saturated-fat and cholesterol intake, increased physical activity (≥150 minutes/week of moderate-intensity activity), weight management, and smoking cessation. To minimize inter-center variability, all investigators receive standardized TLC training materials prior to study initiation. Adherence to TLC recommendations is assessed at each visit using a brief structured questionnaire and is recorded but is not adjudicated as a study endpoint.

## Discussion

3

This study is a multi-center, prospective observational study designed to describe the LDL-C-lowering effectiveness and safety patterns associated with the use of LivaloZet^®^ Tablets (pitavastatin/ezetimibe fixed-dose combination) in patients with dyslipidemia accompanied by metabolic syndrome in real-world clinical settings in Korea. To our knowledge, real-world evidence on pitavastatin/ezetimibe fixed-dose combination therapy in Korean patients with dyslipidemia accompanied by metabolic syndrome remains limited. Specifically, no prospective observational study with a planned enrollment of this scale has been reported for the pitavastatin/ezetimibe fixed-dose combination specifically in Korean patients with dyslipidemia accompanied by metabolic syndrome; this characterization defines the scope of the novelty claim in the present protocol.Although several randomized controlled trials have evaluated the efficacy of pitavastatin/ezetimibe combination therapy in patients with hypercholesterolemia (24–26), real-world evidence in patients with concurrent dyslipidemia and metabolic syndrome remains scarce.

The clinical significance of managing dyslipidemia in patients with metabolic syndrome is well established. Metabolic syndrome, defined by the coexistence of abdominal obesity, hypertension, hyperglycemia, and atherogenic dyslipidemia, substantially amplifies the risk of cardiovascular events beyond that attributable to individual risk factors alone (5, 6). Epidemiological data from Korea indicate that the prevalence of dyslipidemia among adults aged ≥20 years was 37.5%, while that of metabolic syndrome among adults aged ≥19 years was 24.9%, both rising with age (7, 8). Given this epidemiological backdrop and the unmet need for achieving LDL-C targets in Korean patients with cardiovascular risk (27), effective and well-tolerated pharmacological strategies for lipid management in this high-risk population are urgently needed (9).

Statins remain the cornerstone of pharmacological lipid management, and their combination with ezetimibe has been well established as an effective and safe approach for patients who require potent LDL-C reduction or who cannot tolerate high-dose statin monotherapy (9, 11, 12). Prior randomized controlled trials provide the biological and clinical rationale for the present study. The landmark IMPROVE-IT trial demonstrated that adding ezetimibe to statin therapy significantly reduced major cardiovascular events compared with statin monotherapy, providing compelling evidence that non-statin LDL-C lowering translates into clinical benefit (24). Furthermore, the RACING trial confirmed that moderate-intensity statin combined with ezetimibe achieves non-inferior LDL-C reduction with fewer adverse events compared with high-intensity statin monotherapy (25). However, because the present study is a single-arm observational design without a comparator, it cannot replicate the comparative inferences of these randomized trials. Rather, the present study complements such trials by providing descriptive real-world data on routine clinical use. Among statins, pitavastatin is distinguished by its relatively neutral effect on glucose metabolism, compared with several other statins (10, 21–23). Meta-analyses and randomized trials have demonstrated that pitavastatin has a comparatively favorable profile with respect to fasting glucose, HbA1c, and insulin sensitivity, making it a particularly attractive option for patients with metabolic syndrome who frequently have impaired glucose metabolism or established type 2 diabetes (21–23). A recent phase III randomized trial in Korean patients confirmed that pitavastatin/ezetimibe combination therapy achieved superior LDL-C reduction of approximately 52-53% from baseline compared with pitavastatin monotherapy (37-45%), with a comparable safety profile (26). The fixed-dose combination of pitavastatin and ezetimibe in LivaloZet^®^ Tablets is thus a rationally designed therapeutic option that addresses both the lipid-lowering needs and the metabolic concerns of this patient population.

The primary endpoint of this study, the percent change in LDL-C from baseline to Week 24, was selected as the most clinically relevant measure of lipid-lowering effectiveness in routine practice. LDL-C reduction is a well-validated surrogate endpoint for cardiovascular risk reduction, and a substantial body of evidence confirms that each 1 mmol/L reduction in LDL-C corresponds to approximately a 22% reduction in major vascular events (1, 3, 4). The secondary endpoints, including LDL-C changes at Week 48, changes in other lipid parameters (TC, TG, HDL-C, and non-HDL-C; Apo B when available), and the rate of achieving guideline-recommended LDL-C targets, will provide a comprehensive lipid profile assessment over a 48-week treatment period. The achievement of target LDL-C levels stratified by cardiovascular disease risk group is of particular clinical importance, given that real-world data from Korea have consistently demonstrated suboptimal LDL-C goal attainment rates, especially in very high-risk patients (27). Importantly, however, this study does not assess major adverse cardiovascular events (MACE), myocardial infarction, stroke, revascularization, cardiovascular death, or hospitalization. Cardiovascular clinical outcomes are beyond the scope of this 48-week protocol and would require a substantially longer follow-up period and an active comparator to be interpretable; such outcomes should be the subject of future, appropriately designed studies.

Beyond lipid parameters, the exploratory endpoints pertaining to glucose metabolism (HbA1c, HOMA-IR, HOMA-β) and systemic inflammation (hs-CRP) are of considerable scientific interest. The inclusion of these exploratory endpoints reflects the unique metabolic profile of the target population and the well-characterized metabolic properties of pitavastatin (21–23). Pitavastatin has been reported in prior studies to have a comparatively neutral effect on glucose metabolism relative to several other statins (21–23). By descriptively capturing changes in insulin resistance and beta-cell function through HOMA-IR and HOMA-β, this study will describe real-world patterns of the metabolic safety of LivaloZet^®^ Tablets in patients with metabolic syndrome - data that are particularly relevant given that a substantial proportion of enrolled patients are expected to have concurrent pre-diabetes or diabetes. Because exploratory laboratory tests are collected only when available in routine practice, results should be interpreted with caution due to potential non-random missingness. Similarly, monitoring hs-CRP will allow an assessment of patterns in inflammatory markers during pitavastatin/ezetimibe combination therapy.

The observational design of the PIVOT study has inherent strengths and limitations that merit discussion. The principal strength of this design is its ability to capture the real-world use patterns and safety of LivaloZet^®^ Tablets under routine clinical practice conditions, reflecting a diverse and unselected patient population that is more representative of everyday clinical encounters than participants typically enrolled in randomized controlled trials. Observational studies with large sample sizes are increasingly recognized as a critical complement to randomized trials, especially for generating evidence in patient subgroups that are underrepresented in controlled settings, such as patients with multiple comorbidities or complex metabolic profiles. The large planned sample size of 10,000 participants enrolled across multiple centers will provide substantial statistical power for descriptive analyses and subgroup evaluations, and will improve the ability to detect uncommon adverse events. The multi-center design further enhances the generalizability of the findings across different clinical settings throughout Korea.

Nonetheless, the observational nature of this study introduces several important limitations that must be acknowledged. First and most importantly, the absence of a control or comparator arm precludes causal inference and means that the present study cannot establish superiority, non-inferiority, or comparative effectiveness of LivaloZet^®^ versus pitavastatin monotherapy, high-intensity statin monotherapy, ezetimibe combined with other statins, or lifestyle intervention alone, and the results must be interpreted in the context of potential confounding by indication, as treatment decisions are made at the discretion of the treating physician rather than by randomization. Patients prescribed different doses (2/10 mg vs 4/10 mg) or entering with different prior treatment histories may therefore differ systematically in baseline characteristics; pre-specified propensity-score adjusted sensitivity analyses (Section 2.6.5) will address this concern, but residual confounding by unmeasured variables cannot be excluded. Selection bias is a further concern: the voluntary nature of participation and the open-label design mean that participants who consent to enrollment and complete follow-up may differ systematically from the broader real-world target population, being potentially more adherent, more health-engaged, or healthier. Additionally, as optional laboratory assessments - including glucose metabolism parameters, hs-CRP, and ApoB - are collected only when available from routine clinical practice, the completeness of these data may vary across centers and participants, potentially introducing non-random missingness; sensitivity analyses (Section 2.6.4) will address this concern. AST, ALT, and CK, in contrast, are systematically collected at every visit given their clinical importance for statin safety. Although LOCF is a pragmatic approach widely employed in observational studies, it may not fully account for informative missingness; sensitivity analyses using observed cases, multiple imputation, and MMRM (Section 2.6.4) will be used to assess the robustness of the primary findings. Inter-laboratory variability—since lipid panels and safety laboratories are measured at participating centers’ local laboratories—is mitigated by laboratory accreditation requirements and EQA review (Section 2.7), but cannot be entirely eliminated. Finally, this study does not include a comparator arm using other statin/ezetimibe combinations, which limits direct comparative effectiveness inferences, nor does it include cardiovascular clinical outcomes (MACE, myocardial infarction, stroke, revascularization, cardiovascular death, hospitalization), which would require longer follow-up and a randomized comparison to be interpretable. These limitations are inherent to observational study designs and should be considered when interpreting the findings.

In conclusion, the PIVOT study will generate descriptive, prospective real-world evidence on the LDL-C-lowering effectiveness, lipid-target attainment, and safety patterns associated with the use of LivaloZet^®^ Tablets in a clinically relevant and growing patient population — those with both dyslipidemia and metabolic syndrome. The results of this study are expected to inform clinical decision-making in routine practice and to provide descriptive evidence on metabolic safety patterns in patients with concomitant glucose metabolism disorders (21–23). Importantly, the design of this study does not allow for the demonstration of comparative efficacy, non-inferiority, or cardiovascular benefit; such inferences will require future randomized controlled trials with appropriate comparators and clinical endpoints.

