#### Subgroup analyses

2.6.3

Pre-specified subgroup analyses will be performed for the primary endpoint by: (1) cardiovascular risk category; (2) prior lipid-lowering treatment history (treatment-naïve vs inadequate response); (3) dose (2/10 mg vs 4/10 mg); (4) age (<65 vs ≥65 years); (5) sex; (6) presence of diabetes mellitus; and (7) baseline LDL-C (<130 vs ≥130 mg/dL). Subgroup analyses are descriptive; no formal interaction testing is planned.

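### The Discussion credits Section 2.6.5 with a propensity-score safeguard for differences in prior treatment history, but that section plans the adjustment for dose comparisons only

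*Protocol article*

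**What the plan says.** The limitations part of the Discussion (Section 3) names two groupings at risk: "Patients prescribed different doses (2/10 mg vs 4/10 mg) or entering with different prior treatment histories may therefore differ systematically in baseline characteristics". It then states that "pre-specified propensity-score adjusted sensitivity analyses (Section 2.6.5) will address this concern", and concedes residual confounding only by variables that are not measured.

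Section 2.6.5 is narrower. It says that "confounding by indication is a potential concern when comparing outcomes across dose subgroups", and the propensity-score sensitivity analyses "will be performed for dose-stratified analyses". Prior treatment enters only through the covariate list, which after age and sex reads "baseline LDL-C, cardiovascular risk category, prior lipid-lowering therapy, comorbidities".

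Section 2.6.3 lists seven subgroup factors for the primary endpoint, each on its own: risk category, prior treatment history, dose, age, sex, diabetes and baseline LDL-C. It adds: "Subgroup analyses are descriptive; no formal interaction testing is planned".

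Two other places bear on the point. The inclusion criteria (Section 2.2.2) make the treatment-naïve and inadequate-response groups a key subgroup analysis because their LDL-C response may differ. Table 1, footnote 7, allows a baseline lipid value taken on a lipid regulator, provided the regimen had been unchanged for at least 8 weeks.

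**The concern.** The article tells its readers that a pre-specified analysis deals with systematic differences between the two prior-treatment groups. The section it cites contains no such analysis. A reader who trusts the Discussion will take the treatment-naïve versus inadequate-response contrast as backed by an adjusted sensitivity analysis when none is planned.

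There is a related, weaker point. The protocol treats prior treatment as something that may change the response, and the baseline of a pretreated patient may already be lowered by therapy. If the share of pretreated patients differs between, say, risk categories, the mean percent change will differ between those categories even where the response within each prior-treatment group is the same. Section 2.6.3 states no presentation that would let a reader separate the two. The caveat about unmeasured variables does not cover this, because prior medication is recorded.

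**Working it through.** **Step 1: the texts side by side.**

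| | Discussion (Section 3) | Section 2.6.5 |
|---|---|---|
| Groupings named as possibly different | Dose; prior treatment history | Dose |
| Scope of propensity-score adjustment | Said to address both | Dose-stratified analyses |
| Role of prior therapy | A grouping to be compared | A covariate in the dose score |

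Balancing dose groups on prior therapy helps the dose comparison. It does not balance the two prior-treatment groups on anything. No other section of the article supplies an adjusted comparison of them.

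**Step 2: the plan's own precision figure.** Section 2.5 gives 10,000 participants, 20% dropout and SD 22%. 10,000 × 0.80 = 8,000, and 1.96 × 22 / √8,000 = 0.48, which agrees with the stated ±0.5. The SD of 22 is used again in Steps 4 and 5.

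**Step 3: what prior-treatment mix could do (illustration).** The document gives neither the share of pretreated patients in any subgroup nor the response expected in them. Both are assumed.

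- Untreated patients: −52%, the lower end of the 52–53% quoted in the Discussion for the combination in a phase III trial.
- Pretreated patients: from −17% (lower end of the 17–20% quoted in the Introduction for ezetimibe alone) to −40% (assumed). The distance from the untreated response is then 52 − 17 = 35 points down to 52 − 40 = 12 points.
- The response within each prior-treatment group is the same in both subgroups, so there is no true subgroup effect.

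Apparent gap between two subgroups = (difference in pretreated share) × (difference in response).

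| Pretreated share, subgroup A vs B | Responses 12 points apart | Responses 35 points apart |
|---|---|---|
| 40% vs 50% | 0.10 × 12 = 1.2 | 0.10 × 35 = 3.5 |
| 30% vs 60% | 0.30 × 12 = 3.6 | 0.30 × 35 = 10.5 |
| 20% vs 80% | 0.60 × 12 = 7.2 | 0.60 × 35 = 21.0 |

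A second route to the upper end uses midpoints of the trial figures in the Discussion (52.5% for the combination, 41% for pitavastatin alone). The added effect in a patient already on pitavastatin is (1 − 0.525)/(1 − 0.41) − 1 = −19.5%. With shares of 85% and 20% the gap is 0.65 × (52.5 − 19.5) = about 21 points.

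**Step 4: comparison with sampling error.** For two subgroups of 2,000 each (an assumed size), the 95% half-width for the difference is 1.96 × 22 × √(2/2,000) = 1.4 points. Every gap in the table except the smallest exceeds this.

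**Step 5: cost of stratifying.** In a cell of 100 patients, 1.96 × 22 / √100 = ±4.3 points.

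**The case against.** The strongest reply is that this is one loosely worded sentence. The article already analyses the two prior-treatment groups separately, adjusts for prior therapy in the dose comparison, calls all subgroup results descriptive, and disclaims causal and comparative inference. Table layout is commonly left to the analysis plan, which is not shown.

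Much of this stands. The observed mean change in, for example, very-high-risk users is a correct description of those users, and the absence of cross-classified tables from an article is not an error in itself. It does not remove the conflict, however: the Discussion cites Section 2.6.5 by number, and an analysis plan not shown cannot make that section say something else.

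A reader might infer more: that because the propensity score stops at dose, the tables by risk category, diabetes and baseline LDL-C are confounded, with a gap of some 21 points. The document does not support that.

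- The Discussion sentence promises nothing about those tables, and extending the propensity score to prior treatment would not change them.
- The document does not say that higher-risk, diabetic or older patients enter on treatment more often.
- A baseline LDL-C below 130 mg/dL need not be an on-treatment value. Dyslipidemia can qualify on HDL-C or triglycerides alone (Section 2.2.1), and the LDL-C entry levels in the three upper groups of Table 2 start at 55, 70 and 100 mg/dL.
- The 21-point figure needs extreme assumed shares. The version built on the trial midpoints also assumes that all prior therapy had the strength of pitavastatin, although entry allows any lipid regulator.

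**Conclusion.** The contradiction holds on the text alone and needs no assumption: the Discussion claims for the prior-treatment comparison a safeguard that Section 2.6.5 does not contain. It should be corrected.

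The further point is an improvement rather than an error. Differences between subgroups in the unstratified tables may partly reflect prior-treatment mix. The size cannot be derived from the document; under the assumptions shown it lies anywhere from about 1 to about 21 points. It matters only when subgroups are compared with one another. Neither the pooled Week 24 mean nor the description of any single subgroup is affected.

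**What to change.** 1. Reconcile the Discussion with Section 2.6.5 in one of two ways. Either limit the Discussion sentence to dose, or extend Section 2.6.5 to an adjusted treatment-naïve versus inadequate-response comparison. In the second case prior therapy must leave the covariate list, since it is then the grouping being compared. The authors would also have to decide whether baseline LDL-C belongs in the score, because in pretreated patients it may be an on-treatment value. The first option is simpler.
2. In Section 2.6.3, add a presentation of the six factors other than prior treatment within each prior-treatment stratum, or standardised to the cohort's overall prior-treatment mix.
3. Keep the unstratified tables as descriptive results, with a note that differences between subgroups in them may reflect prior-treatment mix.

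Prior lipid-regulator use is already collected (Table 1, footnote 5), so no new data are needed. The cost is a corrected sentence or a short addition to Section 2.6.5, extra tables, and the wider intervals in small cells shown in the working.
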